### 2.6. Measures

#### Sample Characterization Measures

A structured form will be used, with questions about prenatal (gestational and maternal age, number of prenatal consultations, pregnancies, deliveries, abortions, and antenatal corticosteroid use), perinatal (birth weight, Apgar in the fifth minute, and delivery conditions), and postpartum (weight and gestational age at hospital discharge, days of hospitalization and complications, and use of mechanical ventilation and oxygen therapy).

### 2.7. Outcome Measures

#### 2.7.1. Primary Outcome

Assessments of angular kinematics and time for cervical extension will be conducted using the Kinovea^®^ software version 0.9.5 (Joan Charmant & Contributors, Bordeaux, France), which will perform a 2D kinematic analysis of movements recorded during cervical extension in the prone position [24]. This software has adequate reliability, validity, and reproducibility for analyzing dynamic movements [27,28,29]. Goniometry for cervical flexion (0 to 65°) and extension (0 to 90°) will determine the points and plot the angles of cervical extension [30].

Time for cervical extension will be considered when the preterm infant starts cervical extension at 0° and reaches a maximum elevation between 45° and 90°. 

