## Abstract

Purpose: The primary aim will be to assess the effects of prone positioning (tummy time) on cervical extension (angular kinematics and time) in preterm infants. The secondary aim will be to assess the effects of tummy time on gross motor function. Methods: This randomized, controlled clinical trial will include 40 preterm infants weighing less than 2500 g, randomly allocated into control or experimental group (n = 20) and followed up from birth to six months of corrected age by the team of the neonatal follow-up clinic. Caregivers will be routinely guided on bonding, developmental milestones, and how to perform the tummy time for 30 min throughout the day (experimental group). An illustrative booklet will be provided as support material. The hypothesis will be tested using inferential analysis, considering an alpha of 5%. Discussion: We expect tummy time to strengthen cervical muscles needed to overcome gravity, master motor skills, and stimulate the integration between family activity and environmental experiences, considerable challenges to which preterm infants are exposed. Trial registration: Registered in the Brazilian Registry of Clinical Trials (identifier RBR-2nwkr47) on 17 February 2022.

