Tummy time can notably integrate family activity and environmental experiences, considerable challenges to which preterm infants are exposed [20,21]. Mendres-Smith et al. [7] observed that tummy time conducted by parents decreased negative vocalizations and increased exercise tolerance in infants. Thus, this study hypothesizes that tummy time will provide adequate motor development in preterm infants, especially for motor skills in the first months of life. The primary aim will be to assess the angular kinematics of the cervical extension; the assessment of gross motor function will be the secondary aim.

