#### 2.8.4. Assessment

A research team will be responsible for assessments and will be blinded to allocation. Four assessments will be performed: one pre-intervention (baseline) and three post-intervention. The baseline assessment will be at hospital discharge (beginning of the intervention), and the next will be performed at 2, 3, and 4 months of corrected age. Figure 2 shows the study schema.

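### Time for cervical extension, listed under the primary outcome, runs to each infant's own maximum, gives no value below 45° and has no stated direction of benefit

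*Protocol article*

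**What the plan says.** Section 2.7.1 (Primary Outcome) names two measures: "Assessments of angular kinematics and time for cervical extension will be conducted using the Kinovea" software. For the angle, goniometry with "extension (0 to 90°) will determine the points and plot the angles of cervical extension", so a lift below 45° still yields an angle. Time is counted "when the preterm infant starts cervical extension at 0° and reaches a maximum elevation between 45° and 90" degrees. The article gives no value for an infant whose maximum is lower, and it does not say which direction of time is a benefit.

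The status of time differs between sections. The Abstract states the primary aim as effects "on cervical extension (angular kinematics and time) in preterm infants". Section 1 says "The primary aim will be to assess the angular kinematics of the cervical extension" and does not mention time.

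On visits (those after baseline are timed by corrected age), section 2.8.4 states: "The baseline assessment will be at hospital discharge (beginning of the intervention), and the next will be performed at 2, 3, and 4 months". Section 2.3 selects infants with a poor or unusual motor repertoire. Section 2.8.5 plans a split-plot ANOVA and linear mixed models, and replaces missing data with the infant's last value.

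**The concern.** Two features of the definition cause trouble.

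- **The end point moves.** The time measured is roughly height divided by speed. The Abstract expects tummy time to strengthen the neck muscles, so height should rise. A higher lift lengthens the time unless speed rises in proportion. A difference between arms could then mean a higher lift, a slower lift or both, and the article gives no direction by which to read it.
- **There is no value below 45°.** Read literally, passing 45° is a condition for having a time at all. At the visits after baseline the intervention is expected to affect that condition. The infants with a value would then no longer be the randomised groups: the treated arm would include weaker lifters whose counterparts in the control arm drop out. Carrying the last value forward does not help an infant who has never reached 45°, because there is nothing to carry.

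At stake is the interpretation of one of the two measures listed as primary. The angle measure is not affected.

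**Working it through.** **Inputs.** From the article: start at 0°, end at a maximum between 45° and 90° (2.7.1); 20 infants per arm (Abstract); visits at discharge and at 2, 3 and 4 months (2.8.4). The article states no figure for time, so there is none to reproduce. All angle and speed values below are assumptions.

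**Step 1, the moving end point.** Time = maximum angle / speed. At equal speed, 90°/45° = 2. This is the extreme ratio between two infants, not an expected difference between groups.

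**Step 2, selection alone.** Assume the maximum angle is normal with SD 15°, the benefit is 8°, the correlation between angle and speed is 0.5, and treatment has no effect on speed. With a = (45 − mean)/15, the share with a value is 1 − Φ(a). The mean speed of those infants, in SD units, lies 0.5 × φ(a)/[1 − Φ(a)] above that of the whole arm.

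For a control mean of 40°:
- control: a = 0.333, share 0.369, φ/(1 − Φ) = 1.022
- experimental (mean 48°): a = −0.200, share 0.579, φ/(1 − Φ) = 0.675
- apparent slowing = 0.5 × (1.022 − 0.675) = 0.17 SD

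| Control mean | Share with a value, control / experimental | Apparent slowing (SD) |
|---|---|---|
| 30° | 16% / 32% | 0.20 |
| 40° | 37% / 58% | 0.17 |
| 50° | 63% / 81% | 0.13 |
| 60° | 84% / 94% | 0.08 |
| 70° | 95% / 99% | 0.03 |

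This is a shift in speed among infants with a value, before the moving end point is added.

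**Step 3, both features together.** Simulation with 20 per arm: maximum angle normal with SD 20° and capped at 90°; speed log-normal around 30°/s with log-SD 0.25, independent of height; time counted only if the maximum is at least 45°; no true effect on speed.

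| Mean maximum, control / treated | Share with a value | Mean time (s) | Trials in which treated looks slower |
|---|---|---|---|
| 40 / 48° | 40 / 56% | 2.03 / 2.13 | 61% |
| 40 / 55° | 40 / 69% | 2.04 / 2.22 | 76% |
| 45 / 60° | 50 / 77% | 2.09 / 2.30 | 77% |
| 45 / 65° | 50 / 84% | 2.09 / 2.39 | 85% |
| 50 / 70° | 60 / 89% | 2.15 / 2.48 | 90% |

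Without distortion the last column would be 50%. In the four cases with a 15–20° benefit, the treated arm is significantly slower in 8–22% of trials. With a true 5% gain in speed it still looks slower in 61–79% of them; in the 8° case the figure is then about 50%. A speed gain of about 10–20% restores the sign.

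**Step 4, does a fixed end point repair it?** With means of 45/60° and timing to a fixed 45°, no speed effect gives 1.55 s in both arms, and a 5% gain gives 1.55 s against 1.47 s. The article's definition gives 2.09 against 2.30 s and 2.09 against 2.20 s for the same two cases. If speed and height are correlated at 0.6 and every treated infant is 5% faster, the infants who reach 45° still show 1.36 s in controls against 1.38 s in treated. Fixing the end point alone leaves the selection, so infants below 45° also need a value.

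**The case against.** The strongest reply is that the sentence in 2.7.1 is loosely worded. The range 45° to 90° may only mark where the maximum is expected to fall and need not be an eligibility cut. That is a fair reading, and it is why the selection argument is conditional here. It does not save the end point, which is the infant's own maximum on either reading. Nor does it supply a rule for an infant who stays lower.

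Second, the size is wholly assumed. No section gives an angle mean, an SD or an angle-speed correlation, and nothing shows how many infants fall short of 45° at 2, 3 or 4 months. If most pass it, the selection part nearly vanishes, as the 70° row shows. This stands.

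Third, several stronger readings are tempting and go too far:

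- A reader might infer that the measure reverses the direction of benefit. The article states no direction, so there is none to reverse; what is shown is that height and speed are confounded.
- A reader might count missing times at discharge as treatment-related selection. Section 2.8.4 makes that visit the baseline, so treatment cannot have caused them.
- A reader might say that baseline adjustment fails. Section 2.8.5 names none; ANCOVA appears only in the sample size section.
- A reader might take section 1 to make maximum angle the sole primary outcome. It says angular kinematics, which could include timing, and names no maximum.

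Finally, handling rules may be left to a fuller document. But this article fixes the start and end of the clock itself, and that definition is what is at issue.

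**Conclusion.** The concern holds in a limited form. As written, time to the infant's own maximum mixes how high with how fast, has no stated direction of benefit, and, read literally, leaves out infants below 45°, a threshold the intervention is expected to shift. The moving end point follows from the wording alone. The selection effect depends on the literal reading and on how many infants fall short at the later visits: from 0.20 SD at a control mean of 30° to 0.03 SD at 70°, under the assumptions of step 2. An arm difference in the misleading direction is possible but not certain. The documents do not support saying that the primary outcome as a whole fails, since the angle can be measured in every infant from 0° to 90°. The difference between the Abstract with 2.7.1 and section 1 over the status of time is a matter of wording to reconcile, though left open it allows the role of time to be settled after the results are known.

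**What to change.** In section 2.7.1:

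1. Define time as the interval from 0° to first passing a fixed 45°, and state that shorter is better.
2. Keep every assessed infant who does not reach 45° at a visit in the comparison as the worst rank, and compare the arms on ranks. Treat an infant who was not assessed as missing, not as worst rank.
3. Report the share reaching 45° by arm and visit.

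In section 2.8.5, name the rank-based comparison for time, and limit the last-value rule to visits that were not made.

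In the Abstract, section 1 and section 2.7.1, state in the same terms whether time is primary. Making time secondary is optional and not needed for the repair; as the trial is registered, it would be a change of primary outcome and would have to be declared as one.

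**Cost.** The same videos are read and no visit is added. The wording of these sections changes, as does the registry entry if it carries the definition. The price is that time is summarised by ranks or medians instead of a mean. Time to 45° also says nothing about movement above 45°, which the angle measure already covers.

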#### 2.7.2. Secondary Outcome

Gross motor function will be assessed using the Bayley Child Development Scale—III, a gold standard instrument to assess child development. This scale was translated, validated, and adapted for Brazilian children [31]. Standard and composite scores will consider a mean of 10 ± 3 of standard deviation (SD) and 100 ± 15, respectively. Following the qualitative classification of the manual [31], the delay threshold will be 79 points (1.5 SD below the mean), easing the comparison with the expected percentages on the normality curve.

### 2.8. Assessment Procedures

#### 2.8.1. Sample Selection

The sample will be selected at the pediatrics and childcare outpatient clinic. The researcher responsible for the selection will invite all caregivers of preterm infants who meet the inclusion criteria.

#### 2.8.2. Follow-Up

After the first outpatient consultation, a researcher will allocate the preterm infants into control or experimental group and follow-up with them during routine consultations; this researcher will be blinded to the allocation. All preterm infants will also be followed up by telemonitoring. The researcher responsible for the intervention will contact all caregivers weekly to answer questions, schedule evaluations, and encourage participation.

#### 2.8.3. Study Groups

In the control group, caregivers will routinely receive guidance from the care team of the follow-up outpatient clinic (e.g., doctors, nurses, and physical therapists) about bonding and developmental milestones, following the Child’s Handbook [32].

In the experimental group, caregivers will receive the same guidance as the control group and an illustrative booklet on tummy time. The advice will be verbally reinforced to recommend tummy time for 30 min daily throughout the day to 3 months of corrected age [10].

Caregivers will be instructed to conduct and supervise activities while the preterm infants are alert and awake. The preterm infant must be placed on a fixed and comfortable surface to perform the tummy time, and the caregivers must pay attention to signs of tiredness (e.g., crying or resting the face on the surface), ending the practice before the infant gets tired. 

The booklet will be delivered on the first day and will comprise an illustrative guideline on the exercises and the proper type of surface, and a space to record the practice time. The booklet was based on guidelines from the American Occupational Therapy Association [33] (Supplementary Material).

#### 2.8.4. Assessment

A research team will be responsible for assessments and will be blinded to allocation. Four assessments will be performed: one pre-intervention (baseline) and three post-intervention. The baseline assessment will be at hospital discharge (beginning of the intervention), and the next will be performed at 2, 3, and 4 months of corrected age. Figure 2 shows the study schema.

#### 2.8.5. Data Analysis

Data analysis will be performed by a researcher blinded to allocation, using the Statistical Package for the Social Sciences software (IBM, Armonk, NY, USA). Only the primary investigator (not involved in data collection) may stop the study and have access to the final data.

The descriptive analysis will be presented as measures of central tendency and dispersion, and the inferential analysis will consider a statistical significance of 5%. The Shapiro–Wilk test will analyze data distribution. Moreover, the split-plot ANOVA will be used to compare differences between groups and assessments, and linear mixed models will analyze possible differences between groups. Regarding the interventions, the *t*-test for independent samples or the Mann–Whitney test will be used for intergroup comparisons.

Group description will be presented as mean and SD, and the effect size and 95% confidence interval will be reported. The intent-to-treat analysis will be performed for missing data, considering the last data of the preterm infant.

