### 2.2. Sample Size

The sample size was calculated using the G Power software, considering the Ancova test. The randomized controlled pilot study of Flierman et al. [24] was considered to determine the effect size (Cohen’s d). The estimated minimum sample size was 40 preterm infants, considering the gross motor subtest of 9.1 ± 1.7 and 8.1 ± 2.0 (Cohen’s d of 0.59), two groups, four assessments, sampling error of 0.05, and a power of 0.80.

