### 2.5. Randomization and Blinding

Randomization will be stratified by gender and preterm infants will be separated into two groups using a computer-generated randomization sequence [25]. Three researchers, not involved in the study, will be responsible for allocation and assessments of the infants and for data analysis. The allocation will be sealed in opaque envelopes at the assignment and will keep the randomization confidential during the study. The assessments results will not be disclosed to the researcher responsible for the interventions and the data will be tabulated with a predetermined encoding by another blinded evaluator.

Another researcher not involved in the study and blinded to the allocation will conduct all assessments; results will not be disclosed to the researcher responsible for the interventions. The parents will be instructed, previously, not to tell the researcher what kind of orientation they are receiving. Figure 1 illustrates the protocol according to Standard Protocol Items: Recommendations for Interventional Trials (SPIRIT) [26].

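### Section 2.8.5 plans three overlapping group comparisons at 5% for two primary variables without naming a decisive one, and the sizing ANCOVA is not among them

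*Protocol article*

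**What the plan says.** Section 2.8.5 of the protocol article lists three kinds of group comparison. In its words, "the split-plot ANOVA will be used to compare differences between groups and assessments, and linear mixed models will analyze possible differences between groups". A further sentence, introduced as concerning the interventions, says that a t-test or Mann–Whitney "test will be used for intergroup comparisons". One level covers everything: "the inferential analysis will consider a statistical significance of 5" per cent. The Abstract repeats it. Neither place splits the 5% or ranks the tests.

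Four other sections bear on this:

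- **Section 2.2** sizes the trial "considering the Ancova test", with "two groups, four assessments, sampling error of 0.05, and a power of 0.80".
- **Section 2.5:** "Randomization will be stratified by gender".
- **Section 2.7.1**, on the primary outcome: "Assessments of angular kinematics and time for cervical extension will be conducted". That makes two variables. The Abstract also gives angle and time, but the end of the Introduction names angular kinematics alone as the primary aim.
- **Section 2.8.4** fixes four assessments: baseline at hospital discharge, then 2, 3 and 4 months of corrected age.

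**The concern.** Two separate things are at stake.

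**Error rate.** Several tests address the same group question, on two primary variables and at three follow-up visits, and each is read at 5%. Unless one is declared decisive beforehand, a positive finding on any of them can be presented as the trial's result. The chance of that happening with no true effect is then above 5%.

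**Power.** The trial was sized on an ANCOVA, whose usual advantage is that the baseline value enters as a covariate. The split-plot ANOVA named instead treats baseline as one of four outcome levels. No effect can exist at baseline, so averaging it in shrinks the group effect. A trial of 40 infants has little room for that.

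**Working it through.** **1. The plan's own inputs.** The difference is 9.1 − 8.1 = 1.0, with SDs 1.7 and 2.0.

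- 1.0/1.7 = 0.588, which is the stated d of 0.59.
- The pooled SD is √((1.7² + 2.0²)/2) = 1.856, which gives d = 0.539.
- With d = 0.59, α = 0.05 two-sided and 80% power, two means need 92 infants in all. An ANCOVA with no credit for the covariate needs 93.
- A total of 40 follows for a single-visit ANCOVA only if baseline correlates about 0.75 with outcome: 92 × (1 − 0.75²) ≈ 40. Section 2.2 states no correlation.

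Whether 40 is justified is a separate point. It matters here only because, on this ANCOVA route, the baseline must be a covariate.

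**2. False-positive chance.** I simulated 20,000 null trials per setting, with 20 per group, four assessments, complete normal data and two-sided 5% tests. Sidedness is not stated, so two-sided is an assumption. I also assumed a common within-infant correlation of 0.3, 0.5 or 0.7 and a correlation between the two primary variables of 0 or 0.5. The mixed model is represented by the group effect on the mean of the three follow-ups.

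| Tests counted | One variable | Both variables |
|---|---|---|
| Split-plot group effect, mixed-model group effect, 4-month t-test | 0.076–0.093 | 0.14–0.18 |
| Split-plot group effect and interaction, mixed-model group effect, no t-test | 0.10–0.11 | 0.18–0.21 |
| First row plus split-plot interaction | 0.12–0.13 | 0.21–0.25 |
| As above, with t-tests at all three follow-ups | 0.14–0.18 | 0.25–0.33 |

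Each test taken alone held its level (about 0.05).

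**3. Power.** Take unit SD, a difference d at each follow-up and none at baseline, and common correlation ρ. With 20 per group, the variance of a group difference is the per-infant variance V times 2/20.

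- *Split-plot group effect:* the difference is (0 + d + d + d)/4 = 0.75d, with V = (1 + 3ρ)/4 and 38 df.
- *Baseline-adjusted follow-up mean:* the difference is d, with V = (1 + 2ρ)/3 − ρ² and 37 df.

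At ρ = 0.5 and d = 0.59:

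- Split-plot: V = 0.625, noncentrality 0.4425/√0.0625 = 1.77, power 0.41.
- Adjusted: V = 0.4167, noncentrality 0.59/√0.04167 = 2.89, power 0.80.

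| Assumed ρ (d = 0.59) | Split-plot group effect | Split-plot interaction | Follow-up mean, unadjusted | Follow-up mean, baseline-adjusted |
|---|---|---|---|---|
| 0.3 | 0.51 | 0.33 | 0.70 | 0.78 |
| 0.5 | 0.41 | 0.44 | 0.61 | 0.80 |
| 0.7 | 0.34 | 0.68 | 0.53 | 0.90 |

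A single-visit t-test has power 0.44 throughout. With d = 0.539, the split-plot group effect has 0.29–0.44 and the adjusted mean 0.70–0.85.

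**4. A weaker baseline.** Let baseline correlate 0.2 with follow-up, and the follow-ups 0.7 with each other.

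- Split-plot: V = (4 + 6 × 0.2 + 6 × 0.7)/16 = 0.5875, power 0.43.
- Adjusted mean: V = 0.8 − 0.04 = 0.76, power 0.55.
- Unadjusted follow-up mean: power 0.53.

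Most of the advantage from adjustment has then gone.

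**The case against.** The strongest reply is that this is a condensed article. Covariate lists and test hierarchies usually sit in a full protocol or analysis plan, which is not shown. That stands for the mixed model: its covariates are unstated, so it cannot be called unadjusted, and sex may yet be in it. It does not answer the main point. The article itself fixes overlapping tests at an undivided 5%, and it sizes on a method that its analysis section does not list.

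A reader might infer more than the documents support:

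- **That about half the attainable power is lost.** This is true of the split-plot group effect near an assumed correlation of 0.5 (0.41 against 0.80). Over correlations of 0 to 0.8 the relative loss runs from 12% to 67%. It is smaller for a follow-up mixed model (0.61 against 0.80 at 0.5), and the interaction test does better at high correlation. The documents give no correlation.
- **That baseline is ignored.** It is one of the four assessments, and the split-plot interaction uses it. The fault is its role as an outcome level.
- **That omitting baseline or sex inflates the error rate.** It costs power only. For sex the cost is probably small: if sex explained an assumed 10% of variance, adjustment would add about 4 points to the power of a single-visit t-test.
- **That t-tests at all three visits are planned.** The sentence is ambiguous and names no visits. The inflation remains without any t-test (second row of the first table).

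It is also fair to say that d = 0.59 comes from a gross motor subtest. The power figures compare methods and do not predict power for cervical angle.

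**Conclusion.** The concern holds in this form. Section 2.8.5 gives no decisive test, variable or time point, and its methods do not match the ANCOVA in section 2.2 or take up the stratum in section 2.5.

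If any positive test counts, the error rate for one variable is about 0.08–0.11 with a minimal set of tests and 0.14–0.18 with t-tests at every follow-up. Over both variables it is about 0.14–0.33. These figures depend on which tests are run and on the assumed correlations. The inflation comes only from the undesignated tests.

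The power point is separate and conditional. The dilution to three quarters follows from the design if the effect appears only after baseline. How much power that costs depends on correlations the documents do not state: large at a common correlation of 0.3–0.7, modest if baseline is only weakly related to follow-up.

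**What to change.** Reword section 2.8.5, before any group-level results are seen:

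1. Name one primary analysis consistent with section 2.2: a linear mixed model (or ANCOVA) on the post-baseline visits, with group, visit, group × visit, the infant's baseline value and sex, allowing for correlation within infant.
2. Name one contrast at two-sided 5%, for example the group difference averaged over the 2-, 3- and 4-month visits. Other summaries are defensible, provided that one is fixed in advance.
3. Either name one primary variable, or keep both with an adjustment such as Holm. This is the sponsor's choice, but the Introduction (angle only) must then agree with the Abstract and section 2.7.1 (angle and time).
4. Drop the split-plot ANOVA and the t-test or Mann–Whitney comparison as outcome tests, or label them supportive.

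This needs no further infants or visits, and mixed models are already in the plan. The cost is that fewer results can be called confirmatory. If both variables stay primary, Holm also takes some power from each.

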### 2.4. Exclusion Criteria

We will exclude preterm infants diagnosed with grade III and IV intraventricular hemorrhage and those whose caregivers withdraw. After the randomization, we will exclude preterm infants who present any worsening of health and need hospitalization, those who move from the state, who do not attend two evaluations, and those whose caregivers do not answer the phone for three consecutive days to reschedule the assessments.

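### Carrying the last value forward biases the 4-month cervical-extension angle against the arm with more or earlier dropout; the planned mixed model on observed data makes it unnecessary

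*Protocol article*

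**What the plan says.** Section 2.8.5 (Data Analysis) states: "The intent-to-treat analysis will be performed for missing data, considering the last data of the preterm infant". The article names no other method for missing data. The same section lists a split-plot ANOVA for groups and assessments, says that "linear mixed models will analyze possible differences between groups", and adds t-tests or Mann–Whitney tests between groups. It does not say which of these the carried values enter.

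Section 2.8.4 puts the baseline assessment at hospital discharge, and "the next will be performed at 2, 3, and 4 months of corrected age". The primary outcome in section 2.7.1 is the angle and time of cervical extension in prone, measured from video. The secondary outcome in section 2.7.2 is the Bayley-III, on age-normed scales: "Standard and composite scores will consider a mean of 10 ± 3 of standard deviation (SD) and 100 ± 15, respectively".

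Section 2.4 removes some infants after randomisation: those who worsen and need hospitalisation, those who leave the state, and those "who do not attend two evaluations, and those whose caregivers do not answer the phone for three consecutive days to reschedule the assessments".

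**The concern.** Carrying a value forward assumes that nothing changes after the last attended visit. The extension angle is not adjusted for age, and the trial's rationale is that head and neck control develops in these months. A value from an earlier visit placed at 4 months is therefore expected to understate what that infant would have shown.

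If both arms lost the same share of infants at the same times, and growth were the same in both, the understatement would cancel. Unequal loss is plausible, because only experimental-arm caregivers get the advice to "recommend tummy time for 30 min daily throughout the day to 3 months of corrected age". With 20 infants per arm, one dropout is 5% of an arm, so a few can move the primary estimate. Depending on which arm loses more, the plan could hide a real effect or produce one that does not exist.

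**Working it through.** The article states no figure for growth, spread of the angle or dropout, so there is no plan figure to reproduce. The check uses a formula with assumed inputs and a simulation of the same setting.

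**Formula.** Let p be the share of an arm whose 4-month value is carried, and g the mean gain lost between the carried visit and 4 months. Then

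bias in (experimental − control) = pC × gC − pE × gE.

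**Inputs.** From the article: 20 per arm, four assessments, nominal 5% test. Assumed: mean angles of 10, 35, 60 and 75 degrees at the four assessments, SD 15, within-infant correlation 0.5, dropout unrelated to outcome within arm, and a true effect of 8 degrees present at every visit after baseline.

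**Gains lost.** Control: 65 degrees if baseline is carried (75 − 10), 40 from 2 months (75 − 35), 15 from 3 months (75 − 60). Experimental: 73, 40 and 15, because a carried baseline also loses the 8-degree effect.

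**Reading A: every dropout carried, equally likely after each of the first three assessments.** Mean gains lost are gC = (65 + 40 + 15)/3 = 40 and gE = (73 + 40 + 15)/3 = 42.7.
- 10% control vs 20% experimental: 8 + 0.10 × 40 − 0.20 × 42.7 = 3.5. With no true effect: 4 − 8 = −4.0.
- 10% vs 30%: 8 + 4 − 12.8 = −0.8.

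**Reading B: all dropout follows the 3-month visit, so only 3-month values are carried.** Here g = 15 in both arms.
- 10% vs 20%: 8 + 1.5 − 3.0 = 6.5.
- 10% vs 30%: 8 + 1.5 − 4.5 = 5.0.

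**Reading C: dropout as in A, but infants missing two visits are removed under section 2.4.** Only the third of dropouts lost after 3 months is carried.
- Carried share of those kept, control 10%: 0.033/0.933 = 0.036. Experimental 20%: 0.067/0.867 = 0.077. Experimental 30%: 0.10/0.80 = 0.125.
- 10% vs 20%: 8 + 15 × (0.036 − 0.077) = 7.4.
- 10% vs 30%: 8 + 15 × (0.036 − 0.125) = 6.7.

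**Simulation of the same settings** (t-test at 4 months):

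| Reading | Estimate of a true 8, 10% vs 20% | Estimate of a true 8, 10% vs 30% | Null error rate |
|---|---|---|---|
| A: all carried | 3.4 | −0.8 | 0.08 to 0.18 |
| B: 3-month values only | 6.6 | 5.0 | 0.06 to 0.09 |
| C: section 2.4 exclusion applied | 7.3 | 6.7 | 0.05 to 0.06 |

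Formula and simulation agree within simulation noise. If the effect builds up linearly over visits instead, reading B gives about 5.9 and 4.1.

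**Equal dropout.** At 15% in both arms the null error rate stays near 0.05. Under reading A the SD rises from 15 to about 22 and power falls from about 0.39 to 0.20. Under reading C the SD is about 15.1.

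**Other growth rates, in SD units.** With 25% missing in the experimental arm, 10% in control and no true effect, a gain of 0.25 to 1.0 SD per visit gives:
- 3-month value carried: (0.10 − 0.25) × 0.25 to (0.10 − 0.25) × 1.0 = −0.04 to −0.15 SD.
- Baseline carried, three gains lost: −0.11 to −0.45 SD.

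**The case against.** The strongest objection is section 2.4. An infant lost after baseline misses three evaluations, and one lost after 2 months misses two. Read literally, both are excluded and their values are never carried. That leaves reading C, where the bias is modest and the error rate close to nominal. This stands as a limit on the size. It does not rescue the rule, because removing randomised infants conflicts with the intent-to-treat label in section 2.8.5, and the article does not say which provision governs.

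The assumed trajectory is also only an illustration. Section 2.7.1 uses an extension range of 0 to 90 degrees, whereas a normal distribution with mean 75 and SD 15 puts about 16% above 90, and one with mean 10 puts about 25% below 0. Slower growth gives less bias, as the SD-unit range shows.

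A reader might infer three stronger things that the documents do not support:
- That carried values are known to be too low throughout. This is expected only for the angle. For extension time the direction may differ, and age-normed Bayley scores need not rise.
- That the reading A figures are the expected harm. They require carrying infants whom section 2.4 excludes.
- That the test is invalid however dropout falls. With equal dropout its error rate stayed near 0.05.

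**Conclusion.** The point holds in limited form. Carry-forward is the only missing-data rule in the article, and for a raw angle expected to rise with age it biases the 4-month difference against the arm with more or earlier dropout. Equal dropout does not fully remove the problem: an effect that grows over time is still shrunk. For example, 0.59 SD becomes 0.59 × (1 − 0.20 × 1/3) = 0.55 with 20% missing in both arms and the 3-month value carried.

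Under the assumed trajectory, a true 8 degrees is estimated as about 3.4 to 7.3 at 10% vs 20% dropout and −0.8 to 6.7 at 10% vs 30%, depending mainly on whether section 2.4 or the intent-to-treat statement is followed. Growth, spread and dropout are all assumptions. The direction of the bias follows from the rule and the expected rise; its size cannot be fixed from the article. This should be fixed, but the evidence does not make it a fatal defect.

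**What to change.** In section 2.8.5, delete the clause that substitutes the infant's last data. State that the primary group comparison is the already planned linear mixed model, fitted to all observed assessments of all randomised infants, without single imputation.

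Reconcile section 2.4 with this. Infants who miss visits, move away or are hospitalised should keep the data already observed in the primary analysis. Without that change, deleting the carry-forward clause would still not give an analysis of all randomised infants.

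The cost is a sentence or two in each of the two sections, and no new data. The price in assumptions is that the mixed model is valid only if missingness depends on observed data. An optional sensitivity analysis that shifts the missing experimental-arm values downward would show how far the conclusion depends on that.
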